## Abstract

**Background:**

While effectiveness outcomes of eHealth-facilitated integrated care models (eICMs) in transplant and oncological populations are promising, implementing and sustaining them in real-world settings remain challenging. Allogeneic stem cell transplant (alloSCT) patients could benefit from an eICM to enhance health outcomes. To combat health deterioration, integrating chronic illness management, including continuous symptom and health behaviour monitoring, can shorten reaction times. We will test the 1st-year post-alloSCT effectiveness and evaluate bundled implementation strategies to support the implementation of a newly developed and adapted eICM in allogeneic stem cell transplantation facilitated by eHealth (SMILe–ICM).

SMILe-ICM has been designed by combining implementation, behavioural, and computer science methods. Adaptions were guided by FRAME and FRAME-IS. It consists of four modules: 1) monitoring & follow-up; 2) infection prevention; 3) physical activity; and 4) medication adherence, delivered via eHealth and a care coordinator (an Advanced Practice Nurse). The implementation was supported by contextually adapted implementation strategies (e.g., creating new clinical teams, informing local opinion leaders).

**Methods:**

Using a hybrid effectiveness-implementation randomised controlled trial, we will include a consecutive sample of 80 adult alloSCT patients who were transplanted and followed by University Hospital Basel (Switzerland). Inclusion criteria are basic German proficiency; elementary computer literacy; internet access; and written informed consent. Patients will be excluded if their condition prevents the use of technology, or if they are followed up only at external centres. Patient-level (1:1) stratified randomisation into a usual care group and a SMILe-ICM group will take place 10 days pre-transplantation. To gauge the SMILe–ICM’s effectiveness primary outcome (re-hospitalisation rate), secondary outcomes (healthcare utilization costs; length of inpatient re-hospitalizations, medication adherence; treatment and self-management burden; HRQoL; Graft-versus-Host Disease rate; survival; overall survival rate) and implementation outcomes (acceptability, appropriateness, feasibility, fidelity), we will use multi-method, multi-informant assessment (via questionnaires, interviews, electronic health record data, cost capture methods).

**Discussion:**

The SMILe–ICM has major innovative potential for reengineering alloSCT follow-up care, particularly regarding short- and medium-term outcomes. Our dual focus on implementation and effectiveness will both inform optimization of the SMILe-ICM and provide insights regarding implementation strategies and pathway, understudied in eHealth-facilitated ICMs in chronically ill populations.

**Trial registration:**

ClinicalTrials.gov. Identifier: NCT04789863. Registered April 01, 2021.

## Contribution to the literature

Although eHealth-facilitated integrated care models (eICMs) for chronically ill and transplant populations show promise in RCTs, real-world translation remains challenging, calling for sustainable implementation science-powered innovation.Our newly-developed eHealth-facilitated ICM for allogeneic SteM cell transplantation (SMIL*e*–ICM) originated at the intersection of implementation, behavioural, and computer science methods. It will be tested using a hybrid effectiveness-implementation RCT.Our dual focus on implementation and effectiveness evaluation will inform optimisation of the SMILe-ICM while providing insights regarding the implementation pathway, which is understudied in chronically ill populations. Therefore, this study will inform future eICM adoption decisions.

## Background

Increasing evidence shows the potential of eHealth-facilitated integrated care models (eICMs) to improve outcomes in chronically ill populations including solid organ transplant recipients [1–6]. In chronically ill populations, empirical evidence supports the eICM’s effectiveness in view of reducing symptom severity and healthcare utilization (emergency visits and hospitalisations), as well as of increasing quality of life (QoL), survival rates and medication adherence [7–11]. Among patients with blood cancer and allogeneic stem cell transplant (alloSCT) recipients [12], several pilot studies have evaluated the acceptability, usability, and feasibility of eHealth solutions in the form of smartphone symptom management systems [13] and telehealth visits. Also, in following eICM principles to evaluate remote monitoring of adjuvant chemotherapy-related side effects on symptom burden in cancer patients, a recent European multicentre randomised controlled trial (RCT) showed significant improvements in symptom burden, distress, physical and psychological symptoms compared to patients treated according to the standard care model (*p* < 0.001) [4]. However, implementation of the eICM into routine practice remains challenging, as multilevel barriers (e.g., need for specified training, need for regulations of digital solutions by regulatory agencies) currently impede adoption [1].

Due to the chronic nature of their illness, patients with blood cancer and transplant recipients need not only biomedical, but additionally behavioural and psychosocial care. The various mechanisms through with chronically ill persons receive needed care must be addressed and coordinated across the entire care continuum [14–18]. However, as the current model of care focusses on short- to medium-term curative treatment, chronically ill persons are not well served by prevailing acute care models. Focusing primarily on biomedical aspects of care, these are generally episodic, uni-disciplinary and limited regarding self-management support and prevention [19, 20]. To improve outcomes, eHealth-facilitated integrated care models (eICMs) [1–5] correlate well with reduced symptom severity, emergency visits and hospitalisations, as well as increased quality of life (QoL), survival rates and medication adherence [7–11]. As a patient-centred system of care that addresses chronically ill persons’ complex care needs, the eICM guides care providers to improve the continuity of symptom management, relationships and communication across care settings (e.g., home, community health & hospital) and providers [21–23].

The eHealth-enhanced Chronic Care Model (eCCM) conceptually embeds the principles of chronic illness management [21, 22], encompasses eHealth and incorporates multiple CCM building blocks, i.e., self-management support, delivery systems design, clinical decision support, clinical information systems and eHealth education [23]. Further, the eCCM describes how eHealth can power each of those building blocks [24]. For example, its functions include regular monitoring and feedback regarding vital signs, symptoms and/or health behaviour of community-dwelling patients. These not only enhance self-management, but also improve communication between patients and health care providers, thereby potentially shortening reaction time in case of health deterioration [1, 2]. While eHealth is a crucial component of the eCCM, though, its human-delivered elements are equally critical. That is, while the eHealth components greatly expand patients’ capacities to recognise important changes, clinicians retain major roles in care delivery [25]. Still, as many of the patients’ concerns do not require medical expertise, the first-line clinicians managing an eICM are often nurses in advanced roles such as Advanced Practice Nurses (APNs) [26, 27].

With the increasing global burden of chronic conditions, more health care systems are recognizing the need to reengineer systems of care based on principles of chronic illness management and powering them with eHealth. This need is reflected in health care policy guidelines on ICMs and eHealth [28, 29], with eHealth also fuelled by the recent COVID pandemic [30, 31]. Further increasing the interest in assessing electronic Patient Reported Outcomes (ePROs) [32], the evidence base from trials testing the effectiveness of eICM shows promising findings [1, 7, 9, 10].

For most eHealth interventions, implementation issues are substantial: 44–67% of patients discontinue the offered eHealth tools. These problems often reflect mismatches between the technologies and their contexts, particularly their target users’ needs [33–35]. The results include low adoption rates (10–12%) [33, 35] and problems with acceptance (64–86.5%) [34]. Further, many eHealth solutions fail either to base their work on acknowledged theories or to build on empirical evidence: only 26% refer to a theory of behaviour change; and only 11.3% are evidence-based [36, 37]. For the moment, then, studies tend to report on mHealth apps’ problems with system interoperability (i.e., lack of integration with electronic health records (EHR)) [35], reimbursement structures [38], security (often resulting from insecure communication protocols), and lack of privacy policies [39]. These issues hinder adoption (e.g., a site may want to use a tool, but it may not be compatible with their EHR package) and sustainability (e.g., a site may have used a tool, but it isn’t compatible after an update) in daily clinical practice. However, even if they were accepted within a given context, their sustainability would likely be rather limited, as their developers rarely address multi-level barriers, i.e., those at the patient, health care provider and health care organizational levels [1, 2]. Therefore, implementation aspects of eHealth solutions in general and of eICMs in particular have largely been disregarded [25, 34]. Afforded little credibility, even the best are often stranded for years in the wasteland between publication and implementation.

Traversing this ‘valley of death’ will require both methodological innovation and guidance. Even where theory-based intervention development [36] and user-centred design processes are employed during development [40], no guidance is available to instruct promising interventions from trial settings past potential obstacles and pitfalls to long-term real-world use. However, one field of knowledge can help developers produce such guidance. That field is implementation science [41].

### The SMILe project: a two-phase implementation science project

Our project—the development/adaption, implementation and evaluation of an ICM in allogeneic stem cell transplantation facilitated by eHealth (SMIL*e-ICM*)—was designed to anticipate and address these methodological challenges to sustainably reengineer the follow-up care of alloSCT patients in a Swiss and German setting. AlloSCT patients are a growing group with complex care needs. In 2019, 43′581 patients across 51 countries received allogeneic stem cell transplants [42]. Despite improved long-term survival, mortality and re-hospitalisation rates remain substantial, especially in the first year post-alloSCT [43]. In particular, the first months post-alloSCT constitute the most complex phase in terms of life-threatening complications such as infections, acute graft-versus-host disease (aGvHD) and gastrointestinal complications [44–49]. Avoiding re-hospitalisations or at least shortening re-hospitalisation stays will require early detection and treatment of complications [50, 51]. To achieve that goal, alloSCT patients will need to self-manage complex therapeutic regimens; however, non-adherence is common [52–54]. While eHealth has been applied to deliver individual self-management support interventions [55, 56] or caregiver support [57] in alloSCT, the SMILe-ICM is novel. As a full-scale care model, it has the potential, when successfully implemented, to optimise care processes and ultimately improve this vulnerable group’s health outcomes.

SMILe is a two-phase implementation science project (Fig. 1). *Phase A* consisted of contextual and technology acceptance analyses. These informed the development of the SMILe-ICM and its implementation strategies for the first participating centre (University Hospital Freiburg, Germany), where implementation was successful yet no effectiveness data are available at the current time [58–62]. Phase A also guided the care model’s development and adaption for the second participating centre (University Hospital Basel (USB), Switzerland) [63], ([name] et al. Contextspecific adaptation of an eHealth-facilitated, integrated care model and tailoring its implementation strategies – a mixed-methods study as a part of the SMILe implementation science project, Submitted). Phase A, which was completed in February 2021, [58, 60, 63], was theory-based and benefitted from continuous stakeholder involvement. *Phase B,* which will entail the implementation and testing of the SMILe-ICM in the context of the Swiss alloSCT centre (USB), is the focus of this paper.

**Fig. 1 Fig1:**
[figure not shown]
Overview of the SMILe Project’s two phases. Abbreviations. ICM = Integrated care Model; RCT = randomised controlled trial

#### The SMILe-ICM

The development and further adaption of the SMILe-ICM, which was based on a combination of behavioural, computer and implementation science methods, has been reported previously [60–62]. It is a complex, theory-based intervention, the eHealth components of which have been developed and further adapted by applying agile software development processes and a user-centred design approach [59, 62].

As depicted in Fig. 2 and previously reported [60–62], the SMILe-ICM is based on the five building blocks of the eCCM. It consists of *four modules* (i.e., monitoring & follow-up of vital signs, symptoms and health behaviour; infection prevention; physical activity; medication adherence). Self-management support is driven by behavioural change techniques [64]. The SMILe-ICM relies on two delivery methods: (1) a two-component technology part, i.e., a mobile app for patients (SMILeApp) and its corresponding monitoring interface for care professionals (SMILeCare); and (2) a human part, i.e., APNs acting as *SMILe care coordinators* (CCs).Using the SMILeApp, patients can insert 18 relevant parameters (i.e., vital signs and PROs, see Fig. 2) on a daily basis. All data entered to the SMILeApp will be transferred to the stem cell transplant centre. With each patient’s approval, their input can be overseen by their APN/care coordinators via the SMILeCare monitoring interface. This data transfer allows the APNs to monitor, identify and act upon critical values, symptom-related issues or trends based on pre-established cut-offs and risk-adjusted care protocols. Care protocols also specify when other members of the alloSCT team (e.g., responsible physicians, nurses) will be involved [62]. Patients can also view the progress of their entered values in the SMILeApp and read up on important symptoms in the SMILeApp lexicon. In addition, each patient will receive a step counter to assess his/her daily physical activity. Added for the Swiss setting [63], medication adherence is monitored via the SMILeApp asking for daily intake of immunosuppressive medications and all other ones.In addition, the APNs conduct 12 personal consultations at pre-defined timepoints starting 10 days prior to the patient’s stem cell transplantation and extending to 1 year after. The nursing visits posttransplant are planned in conjunction with the routine outpatient clinic follow-up schedule: first weekly, then monthly for stable patients. During these visits, the APN team provides intervention modules on symptom recognition and assessment, infection prevention, physical activity and medication adherence. For the full first year, considering the patients’ needs, the APNs empower and guide them to self-manage and to support behaviour change, informing and supporting them as necessary based on the course of their disease. As key members of the interdisciplinary team, the APN team promotes productive exchanges between team members and strengthens the role of nursing in the continuum of care.

**Fig. 2 Fig2:**
[figure not shown]
The SMILe–Integrated Care Model. Abbreviations. alloSCTs = allogeneic stem cell transplantation; APN = Advanced Practice Nurse;; CC: Care Coordinator; eCCM = eHealth enhanced Chronic Care Model

#### Classification according to the medical device regulation

According to the Medical Device Regulation introduced in May 2021 [65], the SMILeApp will not be classified as a Medical Device as it can only be used to collect data, to visualise inserted values and to read lexicon information, not to provide individualised feedback regarding the entered values [66].

## Methods

### Study aims

This study has two main aims:
**Aim 1** has two parts**:**

**1a.** to evaluate the SMILe-ICM’s effectiveness in view of one primary outcome—re-hospitalisation rate—and seven secondary outcomes—total healthcare utilization costs, total length of inpatient re-hospitalizations, medication non-adherence, treatment burden, health-related quality of life (HRQL), quality-adjusted life year (QALY), acute and chronic GvHD incidence and grade, and overall survival rate. Regarding the primary outcome, we hypothesise that, compared to the usual-care/control group, patients receiving the SMILe-ICM will have a lower re-hospitalisation rate. As for the secondary outcome set, compared to the control group, we expect to see lower total healthcare utilization costs, shorter lengths of re-hospitalizations, lower medication non-adherence (implementation phase of adherence [67]), less treatment burden, better HRQL, higher quality-adjusted life years (QALY), and equal medical outcomes (acute and chronic GvHD incidence, overall survival).
**1b.** to extend objective **1a** by testing for a potential wane-out of the SMILe-ICM intervention effect in view of primary and secondary outcomes during the three-month post-intervention follow-up.
**Aim 2** is to evaluate the SMILe–ICM’s bundle of implementation strategies and assess acceptability, appropriateness, feasibility, and fidelity (implementation outcomes) as well to evaluate the implementation pathway (as viewed by patients and health care professionals).

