The hospitalisation rate consists of two elements: the number of hospitalisations and the period (in years) over which patients are followed up. We conducted simulations using the paramtest software package [76], computing 10′000 iterations of the chosen parameters. Based on the USB’s available data, we set the hospitalization events per patient year to 1.56. The study’s observation period is 15 months (1.25 years). We determined the minimum sample size using the inverse of the effect size in Schenkel et al. [6], i.e., 1.79 [1.31–2.43]. Following Olivier et al.’s guidance [77], we aimed for the upper bound of a small effect size. The simulation is based on a binomial distribution with a shape parameter of 4. Assuming an α level of 0.05, a power of 80% and an effect size of 1.79, a minimum sample size of 52 patients (26 per group) was determined. Based on a refusal rate of 10% and a 15% drop out rate, then, we will aim to recruit a total of 80 patients (40 per group). Considering that approximately 70 adults per year receive *both alloSCT and follow-up* at USB, recruitment will take a minimum of 16 months.

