#### Randomization process

Intervention patients will receive standard care plus the SMILe-ICM. The usual care group (UCG) will receive standard care. Patients will be randomly allocated 1:1 to the intervention group (IG) or UCG at hospitalisation, i.e., approximately 10 days pre-transplant. Randomization will be stratified by risk group according to age (>/< 65 years), gender (male/female) and living alone (yes/no). The concealed randomization procedure will be implemented via the secuTrial® web-based clinical data management system provided by the USB’s Clinical Trial Unit. After randomization and allocation, no further blinding will be feasible in any group. The study’s duration will be from approximately 10 days pre-transplant to one-year post-transplant, with 3 months’ follow-up after cessation of the intervention period to test for a wane-out effect. A CONSORT flowchart for patients is presented in Fig. 4.

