		***Measurement timepoints (T0 – Tz) and days post-Tx***										
**Variables**	**Measurements**	**T0a**	**T0b**	**T1**	**T2**	**T3**	**T4**	**T5**	**T6**	**T7**	**T8**	***Tz***
		**−10**	**30**	**60**	**90**	**120**	**150**	**180**	**240**	**300**	**365**	***455***

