**Secondary outcomes**												
Healthcare utilisation costs	FIMA**©** (10 Items) [83]			**X**	**X**	**X**	**X**	**X**	**X**	**X**	**X**	**X**
	Swiss standardised unit costs [84, 85]			**X**	**X**	**X**	**X**	**X**	**X**	**X**	**X**	**X**
Length re-hospitalizations	FIMA**©** (10 Items) [83] Medical Records, CRF			**X**	**X**	**X**	**X**	**X**	**X**	**X**	**X**	**X**
Medication adherence (implementation & persistence dimension [67])	Electronic Monitoring: MEMS® Button [86]											
	BAASIS**©** (implementation 4 items; persistence: 1 item) [87]		**X**	**X**	**X**	**X**	**X**	**X**	**X**	**X**	**X**	**X**
Treatment burden	PETS**©** (60 items) [88]	**X**			**X**			**X**			**X**	
Health-related Quality of Life	EQ-5D-5L**©** (5 items) [89]	**X**	**X**	**X**	**X**	**X**	**X**	**X**	**X**	**X**	**X**	**X**
Quality-Adjusted Life Year (QALY)	EQ-5D-5L**©** (5 items) [89], value set for Germany EQ-VT v. 2.0 (116)	**X**	**X**	**X**	**X**	**X**	**X**	**X**	**X**	**X**	**X**	**X**
Incidence/grade chronic and acute GvHD	Medical record, CRF		**X**	**X**	**X**	**X**	**X**	**X**	**X**	**X**	**X**	
Overall survival rate	Medical record, CRF		**X**	**X**	**X**	**X**	**X**	**X**	**X**	**X**	**X**	**X**
Conditioning regimen	Medical record, CRF	**X**										
Donor match/type	Medical record, CRF	**X**										
Disease	Medical record, CRF	**X**										
Disease status at transplant	Medical record, CRF	**X**										
If death: Date and cause of death	Medical record, CRF		**X**	**X**	**X**	**X**	**X**	**X**	**X**	**X**	**X**	**X**
If relapse: Date of relapse	Medical record, CRF		**X**	**X**	**X**	**X**	**X**	**X**	**X**	**X**	**X**	**X**

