#### Variables and measurement

Effectiveness outcomes (Table 3) will be assessed in the IG and UCG at the time of inpatient stay and during regularly scheduled outpatient appointments. After completion of the intervention period, a three-month follow-up is planned to assess sustained health outcomes by further assessing effectiveness outcomes in both groups (see also below).

**Table 3 Tab3:** Effectiveness outcomes

Outcome variable(s)	Measure(s) and data collection procedures	Data source and reporter (when applicable)

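### Aim 1b promises a wane-out test for the secondary outcomes, but Table 2 schedules no treatment-burden (PETS) measurement after the intervention ends

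*Protocol article*

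**What the plan says.** Under Study aims, Aim 1a lists the secondary outcomes: costs and length of re-hospitalisation, then "medication non-adherence, treatment burden, health-related quality of life (HRQL), quality-adjusted life year (QALY), acute and chronic GvHD incidence and grade, and overall survival rate". Aim 1b extends that objective by "testing for a potential wane-out of the SMILe-ICM intervention effect in view of primary and secondary outcomes during the three-month post-intervention follow-up". Variables and measurement makes the same commitment: "a three-month follow-up is planned to assess sustained health outcomes by further assessing effectiveness outcomes in both groups". Randomization process gives the purpose of the extra period: the study runs to one year post-transplant, "with 3 months’ follow-up after cessation of the intervention period to test for a wane-out effect". The Analysis section plans a GLMM for Aim 1b with group, time and group-by-time effects.

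Table 2, under "Measurement timepoints (T0 – Tz) and days post-Tx", sets the data collection at eleven time points: T0a, T0b, T1 to T8, and Tz. Treatment burden (PETS, 60 items) is marked at T0a, T2, T5 and T8. The row "Incidence/grade chronic and acute GvHD" is marked at T0b to T8. Neither row is marked at Tz.

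Table 3 describes PETS as a self-report questionnaire with a 4-week recall and gives the electronic health record as the source for GvHD.

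**The concern.** A wane-out test asks whether the difference between groups at the end of the intervention is still there some time later. It needs at least one measurement after the intervention stops. The aims and the measurement text promise this for the secondary outcomes without exception, while the schedule gives treatment burden no such measurement.

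The hypothesis for treatment burden is directional: less burden in the intervention group. The care coordinators' visits run to one year. Whether any benefit lasts beyond that is a real question for this outcome, and data collected to the schedule would not answer it. The practical risks are that a stated analysis is dropped without comment, or that a day-365 contrast is reported as if it spoke to persistence.

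**Working it through.** No sample-size or power formula applies. The check sets the stated aim against the schedule.

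**1. The follow-up period.** The sample-size section gives an observation period of 15 months (1.25 years). Tz is day 455: 455 / 365.25 = 1.246 years, and 1.246 × 12 = 14.95 months, which agrees. The intervention ends at day 365, so Tz lies 455 − 365 = 90 days later, matching the three-month follow-up. It is the only time point after day 365.

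**2. The rows of Table 2.** Each row below has eleven cells, one per time point.

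| Outcome (instrument or source) | Marked at | Marked at Tz? |
|---|---|---|
| Costs (FIMA, unit costs) | T1 to Tz | yes |
| Length of re-hospitalisations (FIMA, record) | T1 to Tz | yes |
| Adherence (BAASIS) | T0b to Tz | yes |
| Treatment burden (PETS) | T0a, T2, T5, T8 | **no** |
| HRQL and QALY (EQ-5D-5L) | T0a to Tz | yes |
| GvHD (record) | T0b to T8 | **no** |
| Overall survival (record) | T0b to Tz | yes |

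The blanks at Tz are unlikely to come from text extraction. Both rows keep all eleven cells and neighbouring rows carry a mark at Tz. The GvHD row and the "Overall survival rate" row share a source and differ only at Tz.

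**3. Can the T8 score stand in?** The note to Figure 3 allows ±7 days. At the latest, T8 falls on day 365 + 7 = 372, and a 28-day recall then covers days 344 to 372, of which only 7 days lie after day 365. A nominal T8 score covers days 337 to 365, all within the intervention. A score at Tz would cover days 427 to 455, all after it.

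**4. Can the model supply the answer?** With no PETS observation after T8, the change in the group difference from T8 to Tz is not identified. A GLMM with time as a continuous trend could be extended to day 455, but that would be extrapolation from the intervention period. It would assume the answer to the wane-out question.

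**5. GvHD.** The schedule has no mark after day 365, but the source is the medical record, and Table 2 already takes survival, death and relapse from that record at Tz. GvHD between days 365 and 455 can be read from the same place.

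**6. Share of outcomes.** Aim 1a names eight secondary outcomes: costs, length of re-hospitalisation, adherence, treatment burden, HRQL, QALY, GvHD and survival. (Its sentence says seven.) One of the eight has a post-intervention gap that cannot be filled later.

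**The case against.** The strongest reply is that this is loose wording in a secondary aim. Neither sentence says that all secondary outcomes are covered, and Table 2 can be read as specifying which ones are. A 60-item questionnaire given at only four of eleven time points may have been left out at Tz on purpose, to spare patients. That would be a legitimate choice, and no document requires a fifth administration. What stands is that neither sentence names an exception, and Aim 1b extends a list that includes treatment burden. If the omission is deliberate, the text should say so.

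Three stronger readings are tempting and are not supported.

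- A reader might infer that Aim 1b cannot be answered for GvHD either. That holds only for the schedule as written, because the data can be extracted later. GvHD is also hypothesised to be equal between groups, so there is no expected benefit to wane. Post-intervention data would show whether equality persists.
- A reader might infer that treatment burden is the outcome closest to the support being withdrawn. The documents do not rank outcomes this way. Medication adherence has its own intervention module, and BAASIS is marked at Tz.
- A reader might take the entirely blank Table 2 rows for re-hospitalisation and the MEMS Button as further gaps at Tz. They are blank at every time point, which fits continuous collection or a lost merged cell, so nothing can be concluded from them.

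**Conclusion.** The contradiction is real and narrow. For treatment burden, following Table 2 leaves no post-intervention data, the loss cannot be made good later, and the Aim 1b effect cannot be estimated. For GvHD there is a schedule inconsistency that chart extraction can resolve. The primary outcome is untouched, as are the Aim 1a comparisons to day 365, where PETS has a baseline and three later measurements.

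This rests on the Table 2 marks as they appear in the text. Figure 3, which also shows the measurement time points, was not available to check. The point should be corrected, but it does not bear on the trial's main conclusion.

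**What to change.** Choose one of two options for treatment burden.

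- **Measure it.** Add PETS to the Tz assessment, where EQ-5D-5L, BAASIS and FIMA are already given. The cost is one more 60-item questionnaire for each patient at that time point and a small amendment.
- **Narrow the aim.** Restrict Aim 1b, and the follow-up sentence under Variables and measurement, by name to the outcomes measured at Tz. This costs only a change of wording, but the trial gives up any statement on whether an effect on treatment burden lasts.

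Data collection is planned to end in March 2024. For patients already past Tz the first option is no longer open, so if that applies to many of them, the second is the sound choice.

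In either case, mark GvHD at Tz and extend the record extraction already made there for survival, death and relapse to GvHD incidence and grade through day 455. State that for GvHD the question is whether equality persists. The cost is a little extra chart review, which can be done retrospectively.
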